#### Secondary outcomes

The Gastrointestinal Symptom Rating Scale (GSRS) [58] will be used to measure GI symptoms.

The Self-Rating Anxiety Scale (SAS) and the Self-Rating Depression Scale (SDS) [59] will be used to assess subjects’ emotional state.

### Data management

Clinical data will be managed using printed and electronic CRF accessible only by the research team. The CRF is the original record and cannot be changed at all. It will be kept by a researcher of the research team. At the end of the trial, two researchers will enter data from the CRF into a computer. The Evidence-based Medicine Center of the CDUTCM will regularly monitor the trial data.

### Data analysis

#### Clinical data analysis

Statistical analyses of the clinical data will be performed using SPSS 20.0 statistical software (IBM Corporation, Armonk, NY, USA) and supervised by a skilled statistician blinded to group allocation. The Kolmogorov–Smirnov test will be used to test the normal distribution of continuous variables. Continuous normally distributed data will be reported as means and standard deviations; continuous non-normally distributed data will be expressed as medians with interquartile ranges. Categorical data will be presented as frequencies or percentages.

For the demographic and clinical information at baseline, the chi-squared test or Fisher’s exact test will be used for comparison of dichotomous data. The two-sample t test will be used for normally distributed continuous data or the Mann-Whitney U test for non-normally distributed data. To compare baseline and post-treatment changes in the same group, we will use the paired t test. Covariance analysis using baseline data as covariates will be used to compare the effects of different interventions on continuous data. In addition, gender differences and age differences may influence the data results. Therefore, in order to avoid the influence of gender, age and other factors on the data, we will also adopt covariance analysis, taking gender, age, and other factors as covariates respectively, and conduct covariance analysis with continuous data. A p value < 0.05 will be considered statistically significant.

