### Sample size

According to the previous studies [45, 46], the mean difference of PSQI scores between acupuncture and sham acupuncture was at least 2.7. We expect the mean PSQI score to decrease by 4.5 points in the acupuncture group and 1.8 points in the control group after treatment. When α was 0.05, 1-β was 0.9, and standard deviation was 3, the calculated sample size was 27. Given that this is a neuroimaging study, sample size requirements in the neuroimaging field should also be taken into account. At present, there is no accepted standard for the sample size calculation of imaging studies. The requirements of imaging studies [47, 48] and previous similar studies [49, 50] suggest that 12–26 individuals in each group is reasonable sample size for data analysis. To allow for potential problems such as subject dropout and invalid imaging data owing to head movements, a sample of 30 patients in each group is considered reasonable.

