#### Primary outcomes

The primary outcomes include MRI indicators and PSQI scale score. This study will focus on the following MRI indicators: the amplitude of low-frequency fluctuation (ALFF), seed-based functional connectivity (FC), cortical thickness, AD, FA, MD, RD, and Glu. ALFF and FC are the most common analysis indicators in fMRI, and their changes can reflect the functional activities of the brain [53]. Cortical thickness is a quantitative index of cortical morphology, which can directly reflect the changes of brain structure [54]. AD, FA, MD, and RD are all important indexes in DTI technology, which can be used to observe the integrity and connectivity of organizational structure [55]. Glu is an excitatory neurotransmitter involved in the occurrence and maintenance of sleep and wakefulness [56].

The PSQI comprises 19 self-evaluation items, among which 18 items generate 7 components. Each component is graded from 0 to 3, and the cumulative score of each component is the total score of PSQI, which ranges from 0 to 21. The PSQI is the most widely used sleep quality rating scale [57].

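### Several covariance analyses of the PSQI, adjusting for baseline, gender, age and unnamed factors in turn, with none named as decisive and none adjusting for the factors together

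*Protocol article*

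**What the plan says.** All of this stands in the protocol article. Under Clinical data analysis, the between-group comparison is introduced as follows: "Covariance analysis using baseline data as covariates will be used to compare the effects of different interventions on continuous data". The section then remarks that "gender differences and age differences may influence the data results" and, to deal with this, adds a second set of analyses: "taking gender, age, and other factors as covariates respectively, and conduct covariance analysis with continuous data". One threshold closes the paragraph: "A p value < 0.05 will be considered statistically significant".

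Under Primary outcomes, "The primary outcomes include MRI indicators and PSQI scale score". The PSQI total is a continuous score, so both covariance statements apply to it.

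The text leaves three things unsettled. It does not say whether the gender and age models also contain the baseline value. It does not say what the other factors are. It does not say which of the results answers the PSQI question.

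**The concern.** The word *respectively* most naturally means one covariate at a time. On that reading the PSQI gets at least three treatment p values (baseline, gender, age), plus one for each further factor, all held to the same threshold. Two problems follow.

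- **Choice of result.** If the models disagree around 0.05, the text gives no rule for which one counts. A favourable model could be cited, and the open-ended list lets more models be added later.
- **Method against purpose.** The added analyses are meant to take out the influence of gender, age and other factors. A model with age alone leaves gender unadjusted, and the reverse. None of the planned models does what the paragraph sets out to do.

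**Working it through.** **1. The plan's own figure.** The Sample size section gives the expected change ("We expect the mean PSQI score to decrease by 4.5 points in the acupuncture group and 1.8 points in the control group after treatment") and the result ("When α was 0.05, 1-β was 0.9, and standard deviation was 3, the calculated sample size was 27"). The difference is 4.5 − 1.8 = 2.7 points, and 2.7 / 3 = 0.9 SD. With a two-sided α of 0.05 and power 0.90:

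n per group = 2 × (1.960 + 1.282)² × 3² / 2.7² ≈ 25.9, so 26 by the normal approximation.

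The exact t calculation gives 27 (power 0.9006; n = 26 gives 0.889). The stated 27 is reproduced, and this point does not touch it.

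**2. Assumptions for the error rate.** The article gives no correlations, so these are assumed: baseline-to-post correlation 0.3, 0.5 or 0.6; age effect 0.2; sex and one other factor without effect; 27 per arm; no treatment effect. Four models are fitted (baseline, sex, age, one other), and the outcome counted is at least one p < 0.05. With 20,000 simulated trials per setting:

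| Correlation | Added models drop baseline | Added models keep baseline |
|---|---|---|
| 0.3 | 7.4% | 6.4% |
| 0.5 | 8.9% | 6.8% |
| 0.6 | 9.3% | 6.9% |

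Other runs of the same setting span 7.4–9.8% (dropped) and 6.3–7.5% (kept). Any single pre-named model stays at about 5%.

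A wider grid (30 per arm, three or four models, baseline correlation 0.3–0.7, other covariates' correlation with the outcome 0–0.3) gives 6.9–11.7% with baseline dropped and 5.7–10.3% with it kept. If the tests were independent, the figures would be 1 − 0.95³ = 14.3% and 1 − 0.95⁴ = 18.5%. These are not reached because the tests share the same outcome data and are strongly correlated.

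**3. Precision.** For covariates uncorrelated with each other, the standard error of the treatment difference is proportional to √(1 − R²). With baseline correlation r and a single other covariate with correlation c, the ratio of a model without baseline to the baseline-only model is √[(1 − c²) / (1 − r²)]. At r = 0.5:

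- c = 0: √(1 / 0.75) = 1.155
- c = 0.2: √(0.96 / 0.75) = 1.131

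The simulation agrees. At 27 per arm, in SD units, the standard error is 0.268–0.274 without baseline against 0.237 for baseline only: 0.268 / 0.237 = 1.13 and 0.274 / 0.237 = 1.16. If the added models keep baseline, their standard errors are 0.233–0.239, so nothing material is lost. The joint model has 0.235.

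**4. Power at the planned effect.** At 0.9 SD, 27 per arm and r = 0.5, the baseline-adjusted and joint models both have power of about 0.96. Models without baseline have about 0.89–0.92.

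**The case against.** The best defence is that the paragraph already has a main analysis. Only the baseline-adjusted model is given the task of comparing the interventions, and the added models open with wording that marks them as extra. Ranking the models and listing the other factors could also be left to an analysis plan that is not shown. This has force, and the missing list alone would not be a finding. What stands is what the article itself fixes: covariates taken one at a time, which does not serve the stated aim, and one threshold for every model with no status given to any of them.

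A reader might go further and infer that the gender and age models omit the baseline score and are therefore imprecise and underpowered. The text does not say that baseline is omitted; the wording also fits adding each factor to the baseline model, and then there is no material loss. Even if baseline is omitted, power at the planned 0.9 SD is close to the targeted 0.90. A larger shortfall appears only with a smaller effect that the article does not plan for. The baseline-adjusted model already in the plan is also about as precise as the joint one (0.237 against 0.235).

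A reader might also infer that the trial's error rate is inflated as planned. It is inflated only if the favourable model may be chosen. The text neither says so nor prevents it.

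Finally, adding age and sex to the primary model is optional in a randomised trial. That is true, but the article itself names them as influential, and if they are to be adjusted for, they belong in one model.

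**Conclusion.** The point holds as a badly stated method with a modest consequence. The article commits to several covariance analyses of a primary outcome without a deciding model, and its one-at-a-time adjustment cannot remove the joint influence of the factors it names.

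If any significant model may be cited, the type I error is about 6–7% with baseline kept and about 7–10% with it dropped, against about 5% for one pre-named model. The loss of precision, a factor of 1.13–1.16 at correlation 0.5, is conditional on baseline being dropped, which the text leaves open. These sizes rest on assumed correlations and an assumed count of four models; stronger covariates or a longer list of factors would raise the error rate somewhat. The change should be made, but nothing here undermines the design or the sample size.

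**What to change.** Replace the two covariance statements with one deciding model for the PSQI: post-treatment PSQI on arm and baseline PSQI, with age and sex entered jointly, reported as an adjusted difference with its 95% confidence interval. Use the same form for GSRS, SAS and SDS, each with its own baseline. Keep baseline in every adjusted model. Name any other factor in advance and label every other adjusted model as a sensitivity analysis.

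The cost is a sentence or two and two degrees of freedom. The plan already intends to use baseline, age and sex as covariates, so no new data are needed. If age and sex turn out not to be prognostic, the loss is negligible: at 30 per arm, SD 3 and correlation 0.5, the standard error goes from 0.674 to 0.686 PSQI points, a factor of 0.686 / 0.674 = 1.02. If each correlates 0.2 with the outcome, it falls to 0.649.

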#### Imaging data analysis

The fMRI data will be preprocessed and analyzed using SPM12 (http://www.fil.ion.ucl.ac.uk/spm/) and CONN toolbox 18b (https://web.conn-toolbox.org/) with MATLAB 2014b (MathWorks, Inc., Natick, MA, USA). The sMRI data will be analyzed using the VBM toolbox within SPM12. DTI data will be processed using FSL Software on Linux. MRS data will be preprocessed using the commercially available software LCModel spectral-fitting package (version 6.3-1 N; Stephen Provencher, Inc., Oakville, ON, Canada). After standard preprocessing of each imaging modality, the following brain activity information will be calculated to examine the neural response to different treatments: the amplitude of low-frequency fluctuation, group independent component analyses, seed-based functional connectivity, cortical thickness, tract-based spatial statistics, and Glu. Finally, Pearson correlation analysis will be used to assess the association between changes in multimodal neuroimaging features and improvements in clinical outcomes in each group. MRI data from patients who received the drugs will be excluded because of the effects of the combination on brain function during the trial.

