There is growing evidence from MRI studies that acupuncture can restore abnormal brain structure, connections, and metabolism in pathological states [30–32]. Both insomnia [33] and GI disease [34] studies have shown that acupuncture can repair abnormal connections in the brain. Previous studies on the mechanism of acupuncture in treating CID have shown that acupuncture affects the activation of brain regions through tactile somatosensory specific stimuli [35, 36]. Acupuncture can regulate the activity of specific brain regions related to sleep experience, such as the prefrontal lobe, temporal lobe, parietal lobule, anterior cingulate, supramarginal gyrus, and precuneus [36–38]. In addition, acupuncture can also regulate cerebral blood flow and neurotransmitter levels such as 5-hydroxytryptamine (5-HT), gamma aminobutyric acid/glutamate (GABA/Glu) in the brain of patients with insomnia [39, 40]. At present, neuroimaging technology has become the mainstream means to study the mechanism of acupuncture treatment of CID. However, no studies have focused on the mechanism underlying the effect of acupuncture on CID with GI disorder. Therefore, a multimodal MRI approach combining fMRI, sMRI, DTI, and MRS is needed to explore the main mechanisms by which acupuncture affects CID with GI disorders.

For these reasons, we designed this multimodal neuroimaging trial. The study aims are as follows: (1) to confirm the efficacy of acupuncture for patients with insomnia and GI discomfort by comparing it with sham acupuncture; (2) to explore the central response mechanism underlying the effect of acupuncture on CID with GI disorders, focusing on cerebral structure, function, and metabolism; (3) to explore a possible correlation between brain activity changes and symptom improvement caused by different acupuncture modes.

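### Brain–symptom correlations are planned separately in each arm and never compared, so they cannot support a statement that the coupling is specific to real acupuncture

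*Protocol article*

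**What the plan says.** The third study aim in the Background is "to explore a possible correlation between brain activity changes and symptom improvement caused by different acupuncture modes". The analysis that serves it stands near the end of Imaging data analysis: "Pearson correlation analysis will be used to assess the association between changes in multimodal neuroimaging features and improvements in clinical outcomes in each group". The method, the two variables (both changes) and the unit of analysis (each group by itself) are therefore fixed. No test of two correlations and no interaction term is named.

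Elsewhere the arms are compared. Under Clinical data analysis, "Covariance analysis using baseline data as covariates will be used to compare the effects of different interventions on continuous data". Under Imaging data analysis, "the following brain activity information will be calculated to examine the neural response to different treatments". The first compares mean clinical scores. The second states a purpose and names no between-arm test. Neither concerns the association between the two kinds of change.

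The significance rule, "A p value < 0.05 will be considered statistically significant", stands under Clinical data analysis. Sample size concludes that "a sample of 30 patients in each group is considered reasonable". MRI data of patients who took drugs are to be left out of the imaging analysis, so fewer than 30 per arm may remain.

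**The concern.** A correlation that is significant in one arm and not in the other is not evidence that the two correlations differ. With 20 to 30 patients per arm, a moderate true correlation is detected in some samples and missed in others. The arms will therefore often disagree when nothing distinguishes them. If per-arm results are the only output for the third aim, a significant result under real acupuncture beside a non-significant one under sham could be taken as a sign that the coupling belongs to real acupuncture. The planned analysis cannot support that statement, whichever way the results fall.

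**Working it through.** **The plan's own figure.** "When α was 0.05, 1-β was 0.9, and standard deviation was 3, the calculated sample size was 27". With a difference of 4.5 − 1.8 = 2.7 and two-sided α, the normal approximation is n = 2 × (1.960 + 1.282)² × 3² / 2.7² = 25.9, so 26 per group. The t-based calculation gives 26.94, so 27. The figure is reproduced if read as per group. It concerns the PSQI mean difference; no size is given for the correlations.

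**Inputs for the check.**
- Patients per arm with usable MRI: 30 planned and 27 calculated (Sample size). The number lost is not given, so 20 to 30 is assumed.
- Significance level: 0.05, stated for the clinical analysis and assumed to apply here, two-sided.
- True correlation r: not in the document. Values from 0 to 0.5 are assumed, **equal in both arms**, with bivariate normal data.

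**Step 1: how often the arms disagree by chance.** If p is the power of the Pearson test in one arm, exactly one arm is significant with probability 2p(1 − p), and real but not sham with probability p(1 − p). Example at n = 27, r = 0.4: p = 0.561, so 2 × 0.561 × 0.439 = 0.493. Simulation of 100,000 pairs of arms gives:

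| n per arm | true r | power, one arm | exactly one significant | real only |
|---|---|---|---|---|
| 20 | 0 | 0.050 | 9.4% | 4.8% |
| 20 | 0.2 | 0.136 | 23.4% | 11.8% |
| 20 | 0.3 | 0.254 | 38.2% | 19.0% |
| 20 | 0.4 | 0.430 | 48.9% | 24.4% |
| 20 | 0.5 | 0.641 | 45.9% | 22.9% |
| 27 | 0 | 0.050 | 9.5% | 4.7% |
| 27 | 0.2 | 0.171 | 28.3% | 14.2% |
| 27 | 0.3 | 0.336 | 44.8% | 22.3% |
| 27 | 0.4 | 0.561 | 49.3% | 24.6% |
| 27 | 0.5 | 0.782 | 34.0% | 16.9% |
| 30 | 0 | 0.050 | 9.7% | 4.8% |
| 30 | 0.2 | 0.184 | 29.9% | 14.9% |
| 30 | 0.3 | 0.370 | 46.7% | 23.2% |
| 30 | 0.4 | 0.610 | 47.7% | 23.9% |
| 30 | 0.5 | 0.827 | 28.6% | 14.2% |

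The rate of disagreement cannot exceed 50%, because 2p(1 − p) peaks at p = 0.5. It falls again at higher r (8.5% at r = 0.6, n = 30).

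**Step 2: a direct comparison.** Fisher's z for two correlations is z = (atanh r₁ − atanh r₂) / √(2/(n − 3)). In the same simulations it rejects in about 5% of trials at every r and n tried. Among the disagreeing results at n = 30 and r from 0.2 to 0.5, only 10–15% show a significant difference between arms.

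Example at n = 30: r = 0.45 in real acupuncture (p = 0.013) and r = 0.25 in sham (p = 0.18). The standard error is √(2/27) = 0.272, so z = (0.485 − 0.255)/0.272 = 0.84 and p = 0.40.

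**Step 3: power of the direct comparison.** Power is about Φ(|atanh r₁ − atanh r₂|/SE − 1.96). For 0.5 against 0 at n = 30: Φ(0.549/0.272 − 1.96) = Φ(0.06) = 52%. For 0.5 against 0.2: Φ(0.347/0.272 − 1.96) = Φ(−0.69) = 25%. At n = 20 these fall to 36% and 17%. They approximate the power of an interaction test, which compares slopes rather than correlations.

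**The case against.** **The aim can be read more modestly.** It is worded as exploration and does not ask outright whether the modes differ. If it means only that the correlation is to be described under each mode, per-group correlations answer it. This stands: the defect bites only when something is said about one mode against the other. But the wording ties the correlation to the different modes, and the plan offers nothing else to support such a statement.

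**Stronger readings are not supported.** A reader might infer any of the following:
- That the arms are never compared. They are, on clinical means by covariance analysis; only the correlations are not.
- That the whole mechanism question fails. The correlations serve the third aim, while the second aim, on the central response, rests on the imaging measures themselves.
- That the protocol will treat a split result as proof of specificity. It states no such rule; that misreading is a risk, not a plan.
- That the split to fear occurs in nearly half of cases. That figure counts both directions; real significant and sham not is half of it.
- That the number of correlations tested, or the lack of a rank-based alternative, is a further error. The article does not say that every indicator is crossed with every scale, and such details may be left to the full plan.

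**The remedy is weak.** An interaction at this size will often be inconclusive, and imaging change is measured after randomisation, so randomisation does not protect the comparison of slopes. Both points are right. They argue for an estimate with its interval and an exploratory label, not for two separate tests.

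**Conclusion.** The point holds in a limited form. The article fixes within-arm correlations and no comparison of them, so they cannot support a claim that brain–symptom coupling is specific to real acupuncture. With equal true correlations of 0.2 to 0.5 and 20 to 30 patients per arm, exactly one arm is significant for about 23–49% of measure–scale pairs, and the real-only pattern appears for about 12–25%. With no true correlation the figures are about 9–10% and 5%. These sizes rest on assumed correlations, an assumed number of usable scans, normal data and a two-sided 0.05 level carried over from the clinical analysis. The comparison of PSQI between arms is unaffected. This is an inexpensive improvement to an exploratory analysis, not a flaw in the trial's main comparison.

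**What to change.** For each imaging indicator, fit one model to all randomised patients with usable MRI:

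clinical change = arm + imaging change + arm × imaging change + baseline clinical score

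Take PSQI as the lead scale. Base any statement about a difference between arms on the interaction estimate with its 95% CI, labelled exploratory. Keep the per-arm Pearson correlations as description only, and state that significance in one arm alone will not be read as a difference between arms.

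The cost is a few sentences in the analysis plan, with no new data, visits or patients. The price in interpretation is a wide interval at 20 to 30 per arm, and a result that shows association and does not establish a mechanism.

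### The brain–symptom correlations for aim 3 are left unadjusted for age and sex, which the plan itself says may influence the data; a minor, cheap improvement to an exploratory aim

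*Protocol article*

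**What the plan says.** Aim 3 in the Background is "to explore a possible correlation between brain activity changes and symptom improvement caused by different acupuncture modes". The method for it is the next-to-last sentence of Imaging data analysis: "Pearson correlation analysis will be used to assess the association between changes in multimodal neuroimaging features and improvements in clinical outcomes in each group". That is a two-variable correlation of changes, run separately in each arm, with no covariates.

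Clinical data analysis treats continuous outcomes differently. "Covariance analysis using baseline data as covariates will be used to compare the effects of different interventions on continuous data" The section then says that "gender differences and age differences may influence the data results", and answers this with further models "taking gender, age, and other factors as covariates respectively, and conduct covariance analysis with continuous data". Nothing carries either adjustment over to the correlations.

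The arms are small. Under Sample size, "a sample of 30 patients in each group is considered reasonable". Imaging data analysis also drops the MRI data of patients who took drugs, so 30 per arm is an upper limit. The Inclusion criteria admit ages 18 to 65 and any gender.

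**The concern.** One of the two variables in each correlation is the same clinical outcome for which the plan thinks age and sex matter enough to adjust. If older patients, or one sex, improve less on the PSQI and also show smaller change in an imaging feature, the two changes correlate even when neither has anything to do with the other. Aim 3 would then report brain change going with symptom improvement when the common factor is age or sex.

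Baseline severity is a second possible common factor, since a change score contains its own baseline. Whether this distorts a change–change correlation, and whether adjusting for baseline cures it, depends on how the two measures behave over time. The working therefore treats it separately.

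**Working it through.** **The plan's own figure.** The only calculated size is for the PSQI comparison, where Sample size assumes falls of 4.5 and 1.8 points in the two arms. Its result reads: "When α was 0.05, 1-β was 0.9, and standard deviation was 3, the calculated sample size was 27". The difference is 4.5 − 1.8 = 2.7. Two-sided, n = 2 × (1.960 + 1.282)² × 3² / 2.7² = 25.9, so 26 per group by the normal approximation. The t-test calculation gives 27 (power 90.06%). The figure reproduces per group and is not at issue. I use n = 27 below as a realistic size for one arm.

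**Inputs that are assumptions.** The documents give none of these:
- rho, the pre–post correlation, taken equal for both measures; 0.5 unless stated.
- r0, the correlation between baseline PSQI and the baseline imaging feature.
- a, the correlation of age with the follow-up residual of each measure; 0.4 unless stated. A sex effect acts in the same way.

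The two changes have no true link in any case below.

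**Two null models, unit variances.**

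*Autoregressive:* follow-up = rho × baseline + residual. The covariance of the changes is (1 − rho)² r0 + a²(1 − rho²) and each change has variance 2(1 − rho). So r = (1 − rho) r0/2 + a²(1 + rho)/2.

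*Stable trait:* each visit = trait + visit noise, with the traits correlated so that r0 is the same at both visits. The trait cancels in the change. So r = a²/2, whatever r0 is.

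**False-positive rate.** With m = atanh(r) × √(n − 3 − k) for k covariates, the two-sided rate is about Φ(m − 1.96) + Φ(−m − 1.96).

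| Null case, n = 27, rho = 0.5 | Induced r | Rate, raw Pearson |
|---|---|---|
| Trait, a = 0.4 | 0.16/2 = 0.08 | 6.8% |
| Autoregressive, a = 0.4, r0 = 0 | 0.16 × 0.75 = 0.12 | 9.1% |
| Autoregressive, a = 0.4, r0 = 0.5 | 0.125 + 0.12 = 0.245 | 23% |
| Trait, a = 0.2 | 0.04/2 = 0.02 | 5.1% |
| Autoregressive, a = 0.2, r0 = 0 | 0.04 × 0.75 = 0.03 | 5.3% |

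Simulation agrees: 7.0% for the first row and 23.8% for the third. So the 24% is age and correlated baselines together. Age alone at a = 0.4 gives about 7% to 9%, and at a = 0.2 almost nothing.

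**Adjusting the changes for age and sex.** In the trait model r returns to 0; the simulated rate falls from 7.0% to 4.8%. In the autoregressive model with r0 = 0.5 the variance of each change falls by 0.12, so r = 0.125/0.88 = 0.142 and the rate is about 10%; simulation gives 23.8% falling to 10.2%. What remains is the baseline part.

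**Adjusting for both baselines as well.** In the autoregressive model this restores about 5% (simulated 4.6% to 5.3%). In the stable-trait model it creates a correlation. Given both baselines, the sum of the two measures has residual variance proportional to (1 + r0) − (rho + r0)²/(1 + r0), and the difference to (1 − r0) − (rho − r0)²/(1 − r0). At r0 = 0.3 these are 1.3 − 0.64/1.3 = 0.808 and 0.7 − 0.04/0.7 = 0.643. The partial r is (0.808 − 0.643)/(0.808 + 0.643) = 0.11. Simulated rates with no age effect:

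| Trait model, n = 27 | Raw | Adjusted for both baselines |
|---|---|---|
| rho = 0.5, r0 = 0.3 | 4.9% | 8.5% |
| rho = 0.5, r0 = 0.4 | 5.3% | 12.7% |
| rho = 0.5, r0 = 0.49 | 5.0% | 21.5% |
| rho = 0.7, r0 = 0.5 | 5.1% | 8.8% |

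So adjustment for age and sex helps in both models. Adjustment for baseline helps in one and harms in the other.

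**The case against.** **Aim 3 is exploratory, the age and sex sentence sits under clinical data, and an article may leave covariates to the full plan.** The first two points stand. There is a difference of approach between two sections, not a contradiction, and nothing here touches the baseline-adjusted PSQI comparison. The third stands only in part: the article names the method for aim 3, so the comment is on a stated choice.

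**Every size rests on assumed inputs.** This stands. With no age or sex effect, and uncorrelated baselines or stable traits, the planned Pearson correlation is valid.

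A reader might also infer three stronger things that the documents do not support:

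- *That baseline-adjusted week-4 values should replace raw changes.* The documents do not say which model holds, and under stable traits the replacement rejects too often. Nor do they supply r0: the Discussion looks for abnormal brain measures in patients, which is not a gradient of PSQI with a brain measure among patients.
- *That the unadjusted analysis loses precision, worth about a third more patients.* That figure comes from the variance of a change score in a comparison of means. A correlation has no scale: under the null at n = 30 its sampling SD was about 0.18 raw and 0.20 adjusted for baselines, age and sex. Power can be lost if baseline explains much of the change (56% against 77% in one assumed case), but the gap nearly closes (73% against 77%) when r0 = 0.3, where part of the raw figure is the baseline artefact.
- *That correlated baselines cause a large distortion.* Under the autoregressive model the induced r is about 0.02 to 0.18 for r0 of 0.2 to 0.5 and rho of 0.3 to 0.8.

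**Conclusion.** The point holds in a limited form. The plan regards age and sex as possible influences, adjusts the clinical comparisons for them, and leaves them out of the correlations that serve aim 3. With an assumed age correlation of 0.4 with both residuals, false positives at n = 27 are about 7% under stable traits. Under the autoregressive model with rho = r0 = 0.5 they are about 24%, including the baseline part. With a weaker age effect the excess due to age is negligible.

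On baseline the position is unresolved. Correlated baselines can induce about (1 − rho) × r0/2 under one plausible model and nothing under another, so neither the raw nor the baseline-adjusted correlation is safe alone. This is a minor improvement to an exploratory aim.

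**What to change.** In Imaging data analysis, make the aim 3 analysis a partial correlation of imaging change with clinical change in each group, adjusted for age and sex, and rank-based where the normality check fails. Add a sensitivity analysis that also adjusts for the baseline values of both measures, and state that a correlation will be interpreted as mechanistic only if the two agree.

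The cost is a sentence or two and no new data: baselines are measured, and age and gender are already planned covariates. The main analysis gives up two degrees of freedom (25 to 23 at n = 27) and the sensitivity analysis four (25 to 21), which raises its critical |r| from 0.381 to 0.413. Requiring agreement will leave some correlations without a mechanistic reading, which suits an exploratory aim.
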